#### Active transportation

Active transportation (mode and duration in hours and minutes) will be assessed using GPS data from the app, using only registrations that participants have marked as valid. In addition, attitudes towards active transportation will be assessed using the psycho-social measures in section B of the validated Transport and Physical Activity Questionnaire (TPAQ) [37]. Participants are asked to what extent they agree (i.e., strongly agree, somewhat agree, neither agree nor disagree, somewhat disagree, or strongly disagree) to 20 statements regarding walking (10 statements) and cycling (10 statements) as transportation. Examples of statements are: “Walking/cycling to travel from place to place is something I do automatically without really thinking about it.”, “Walking/cycling for travel is enjoyable.” and “It is possible for me to walk/cycle for travel”.

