### Randomisation and blinding

Upon completion of baseline measures, participants are randomised to the intervention or the control group in a 1:1 ratio. A computer-generated random allocation sequence list (in blocks of two) is generated in Stata 13 (StataCorp LP, College Station, Texas, USA). To ensure allocation concealment to study personnel until group allocation, the allocation list is monitored by a member of the research group with no participant contact. After randomisation, participants receive an email containing information about their group allocation. Assessors of the primary and secondary outcomes are blinded to group allocation; however, due to the design of the study participants are not blinded to their allocation.

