#### Development and content

##### The TRAvelVU app

TRavelVU, an automatised and objective assessment of travel behaviour was developed by Trivector AB ©, a company with expertise in sustainable and active transportation. Once downloaded, the TRavelVU app continuously and passively (without manual input) collects data in real time on location and travel speed (GPS). When the user is in motion, the app starts to send GPS data to the server, and these data are transferred into speed and acceleration profiles. The analysed data are then immediately sent back to the app where participants can view their journey (distance, route and suggested mode of transport). The users enter data about their destinations in the app and edit modes of transportation and start/stop times of trips if these have been registered incorrectly. Once a location has been added to the app by the user (e.g., “home” or “office”), TRavelVU remembers this and automatically suggests this destination for future trips. Algorithms are based on a fuzzy logic approach on a number of different variables (e.g., mean speed and percentile speed), to identify the most likely modes of transportation for trip segments [24, 25]. The app has been developed with the aim of minimising battery consumption. All participant data are anonymous and linked to a unique identification number. Using these data, TRavelVU provides detailed information on the participant’s travel behaviour. Fig. 2 shows a screenshot of a daily summary of travel modes for a user in TRavelVU.

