##### Behaviour change program (the TRavelVU plus app)

The behaviour change program in the TRavelVU Plus app was developed by Trivector AB © and researchers with experience in behaviour change interventions (obesity, physical activity and transport). The intervention is grounded in Social Cognitive Theory [26] and Social-Ecological [27] principles. To improve the reporting of the content in behaviour change interventions the behaviour change technique taxonomy is recommended [28]. Thus, key behaviour change techniques known to promote physical activity behaviour are included in the app’s features and text messages (e.g., general information about physical activity and active transport, information regarding consequences, barrier identification, specific goal-setting strategies and functions, self-monitoring and feedback on performance) [28]. See Table 1 for theoretical domains, behaviour change techniques and examples of messages. We also considered recommendations from previous research regarding message linguistics (e.g., grammar, spelling, and positivity), dosage, length as well as timing of delivery [29, 30]. Thus, participants receive 4–6 messages per week that contain no more than 200 characters. The program consist of a core set of messages scheduled to be sent at fixed time points throughout the intervention that all participants receive. The messages include practical tips, general information and strategies for behaviour change. The messages can be accessed at any time throughout the intervention and are organised so that the content follow the study timeline. Thus, in the beginning of the intervention messages provide information about features within the app and strategies for goalsetting, and later on the messages focus on past successes and strategies for sustained behaviour changes. The goalsetting feature allows participants to set weekly individual goals for active transportation (i.e., walking and cycling). Feedback is provided in graphical format, where participants can follow their daily and weekly achievements and as a summary of all previous goals (see Fig. 3). During the week a coloured symbol (red, yellow, or green) guides the participants if their present achievement thus far in time spent in active transportation is enough to reach their goal or if greater efforts are needed. Additionally, at the end of each week a feedback message is sent out, which is tailored and varied according to participants’ goals and level of goal achievement in hours and minutes (i.e., ≥100%, ≥70, < 70% or no goal was set).

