Based on the feedback from the pilot study, the app was revised. The updated app allows participants to accept a registered day as valid even if locations have not been specified (e.g., if one stopped to talk to a neighbour for 3 min during a longer walk). In regards to the manual the participants receive, we clarified how to edit trips manually and that greater battery consumption will occur when using the app. Furthermore, within the manual the study aim was highlighted (i.e., to increase physical activity through active transportation and not through exercise) so that the expectations of the study would be clear for the participants. After the pilot study and discussions within the research group minor changes were made to the wording of the messages and the number of messages were condensed from 87 to 61 to conform to the number needed during the intervention.

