#### App usability and quality assessment

To assess the participant’s use of the app we will collect data on the number of registered days (i.e., days the participants marked as valid in the app) for both groups. For the intervention group the number of weekly goals that were set will be assessed and if goals were met, based on the feedback messages delivered. To assess usability and perceived quality of the TRavelVU Plus app, semi-structured interviews will be conducted in a sub-sample of participants who complete the intervention.

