## Discussion

The SCAMPI trial aims to evaluate the effectiveness of a 3-month behaviour change program delivered via a smartphone app to promote active transportation (i.e., walking and cycling) in adults aged 20–65 years. Active transportation has great potential to increase physical activity levels and thus influence the health of many people; however, interventions targeting travel behaviours are few. To the best of our knowledge, SCAMPI is the first study to assess a smartphone app to deliver such an intervention.

The SCAMPI study has many strengths, including the randomised controlled design and the relatively large population based sample. This design will enable us to assess travel behaviour and intervention effectiveness in a heterogeneous sample representing both urban and non-urban areas in the Stockholm County. Furthermore, the use of objective measures for both physical activity (accelerometers) and travel behaviour (TravelVU app) will provide unique data extending previous research on this topic that have been limited to self-reported data [46]. The novelty of SCAMPI is the development of a smartphone app including a behaviour change program to support participants to engage in active transportation. To date, we found one prior study using an app to promote active transportation as part of a larger campaign; however, the web based app in that study targeted a selected population and used a non-randomised design that did not enable the effectiveness of the app to be assessed [20]. The urgent need to find effective solutions to decrease the alarmingly high levels of sedentary behaviour among adults makes the focus on active transportation valuable. Active transportation may be an attractive option for people to accumulate physical activity time in their everyday life, who otherwise would be inactive. The TRavelVU Plus app therefore has the potential to make a difference on health outcomes for those in greatest need of this change.

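### Active transportation counts only days that unblinded participants marked valid, and they can edit them, so the arm difference can mix travel with logging behaviour

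*Protocol article*

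**What the plan says.** The section on active transportation takes mode and duration from the app's GPS data, "using only registrations that participants have marked as valid". Marking is something the participant does, and the unit is the registered day: the section on app usability counts the "number of registered days (i.e., days the participants marked as valid in the app) for both groups", and the pilot study section reports that "The updated app allows participants to accept a registered day as valid even if locations have not been specified". The description of the TRavelVU app adds that users can "edit modes of transportation and start/stop times of trips if these have been registered incorrectly".

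On blinding, the article says that "Assessors of the primary and secondary outcomes are blinded to group allocation" and, in the same sentence, that "due to the design of the study participants are not blinded to their allocation". The Discussion lists as a strength "the use of objective measures for both physical activity (accelerometers) and travel behaviour (TravelVU app").

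The arms use the app differently. Intervention participants set weekly goals for active transportation, receive goal-related feedback at the end of each week, and during the week see how "a coloured symbol (red, yellow, or green) guides the participants if their present achievement thus far in time spent in active transportation is enough". Controls get a plain summary unrelated to any goal and no behaviour change content. The additional features are withdrawn after 3 months.

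**The concern.** Randomisation protects a comparison when the rule that decides which data count does not depend on what happens after allocation. Here it does. A day enters the outcome if the participant marks it, and the minutes in it can be changed by the participant's edits. One arm is asked to pursue a target expressed in those minutes and is shown its progress. The other arm is not.

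That gives intervention participants more reason to open the app, review the day, add a missed walk or correct a misclassified ride. It may also change how often, and on which days, they mark a day valid. If so, part of any arm difference in active transportation reflects logging. Time in active transportation is the behaviour that the programme targets, so a positive result would naturally be read as evidence that the app changed travel. As defined, the outcome cannot separate that reading from better or more selective record-keeping.

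**Working it through.** **The plan's own figure.** The only sample size given is for MVPA: difference 10 min/day, SD 25, two-sided 0.05, 80% power. Per arm, n = 2 × (1.960 + 0.842)² × 25² / 10² = 98.1, so 99 against 100 stated. Power at 100 per arm is 80.7% (80.4% with the noncentral t), and 200 / (1 - 0.20) = 250. These reproduce and are not in dispute. No figure is given for active transportation, so every input below is an assumption.

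**Selective marking in one arm.** Assume a within-person daily SD of 30 min, a share p of days marked, and a correlation r between active minutes and the latent tendency to mark the day. The mean of marked days exceeds the mean of all days by r × 30 × φ(z_p) / p, where z_p is the normal quantile of p.

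| p | r = 0.1 | r = 0.2 | r = 0.3 |
|---|---|---|---|
| 0.6 | 1.93 | 3.86 | 5.80 |
| 0.8 | 1.05 | 2.10 | 3.15 |

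If r is instead the correlation with the yes/no mark itself, the excess is r × 30 × √((1 - p)/p). For r from 0.1 to 0.3 that is 2.4 to 7.3 min/day at p = 0.6 and 1.5 to 4.5 at p = 0.8. With no selection among controls, these excesses are the spurious arm difference.

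**Selective marking in both arms.** Take the latent form with r = 0.2 in both arms, 60% of control days and 80% of intervention days marked. The difference is 2.10 - 3.86 = -1.8 min/day, against the intervention. The sign depends on the assumptions.

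**Simulation with a true effect of zero.** Assumed: 100 per arm, seven days, mean 40 min/day, between-person SD 20, within-person SD 25, 70% of days marked, 1,000 runs. In the intervention arm only, days above the person's own median are marked more often by the stated number of points and the other days less often by the same number; edits multiply logged minutes.

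| Intervention-arm logging | Spurious difference (min/day) | False-positive rate |
|---|---|---|
| No tilt, no edits | 0.1 | 5% |
| 5-point tilt | 1.2 | 6% |
| 10-point tilt | 2.9 | 15% |
| 20-point tilt | 5.6 | 40% |
| Edits add 5% | 2.0 | 8% |
| Edits add 10% | 3.8 | 21% |
| 10-point tilt and edits add 10% | 7.4 | 58% |

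**If unmarked days counted as zero minutes.** With a mean of 40 min/day and 70% of control days marked, a share of 80% in the intervention arm shifts the difference by 40 × (0.80 - 0.70) = +4 min/day; a share of 60% shifts it by -4.

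**Safeguards in the article.** Multiple imputation and delta-adjustment deal with missing values; they do not touch edited entries. No comparison of marked with unmarked days, or edited with unedited records, is described. Registered days are collected in both arms, but for describing app use and for the per-protocol analyses. The limitation in the Discussion concerns controls changing their travel because they see it, which would dilute the effect; it does not cover differential logging.

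**The case against.** Several points on the other side stand.

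- That goals change marking and editing is an inference. A reader might infer that the symbol and goal feedback count only days marked valid, which would reward marking directly. No passage says so: the app returns analysed data at once and feedback runs through the week. The incentive to edit is the better supported one.
- A reader might infer that the outcome is biased in favour of the intervention. Controls also see their active-transport summary, and the calculation with selection in both arms shows that the sign can reverse.
- A reader might infer that single walks can be picked out for validation. Marking is by day; only editing is by trip.
- Edits correct genuine errors in mode, and the valid mark is the only described sign that a day's record is complete. Battery drain is a reported problem, so unmarked days may be partial. A reader might conclude that raw GPS data should replace the definition; the documents do not show that this would be better.
- Reporting registered days by arm would reveal different marking rates, though not which days were marked or what was edited.
- Staff who process the app data may well be blinded, and the article openly says that participants are not.

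It can also be said that handling of app data belongs in the full protocol or analysis plan. That covers windows and cleaning rules. It does not answer the point, because the article states the valid-mark rule itself.

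**Conclusion.** The point holds in a limited form. A stated rule lets a post-randomisation act by unblinded participants decide which days enter a between-arm comparison, their edits can change the minutes, and only one arm has goals tied to those minutes. The arm difference in active transportation can therefore mix travel with logging.

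Direction and size cannot be known from the documents. Under the assumed inputs, the distortion is a few minutes per day in either direction. For scale only, the trial is powered for 10 min/day of MVPA.

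The reach is limited. Accelerometer MVPA does not depend on app marking. Baseline logging precedes randomisation. The concern is greatest at 3 months and weaker at 6 months, when the goal features have gone. Nothing here shows that a positive result would be false, and the article lists active transportation first among its secondary outcomes without ranking it as the main one. What changes is how far a positive finding can be read as changed travel, and that justifies a change to the plan.

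**What to change.** Before app data are examined by arm:

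1. Keep the valid-marked definition if preferred, and prespecify a companion analysis of all recorded days regardless of the mark, using the app's automatic, unedited classification where it is stored. Use the same seven-day accelerometer windows at 0, 3 and 6 months in both arms.
2. Report, by arm and time point, the number of days marked valid and the number of edits.
3. Claim an effect on active transportation only if the two analyses agree, with agreement defined in advance.
4. Qualify the description of the app measure as objective, and the blinded-assessor statement, for this outcome: participants validate and can edit the record, whoever processes it later.

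The cost is one additional data extract from the app server, one additional analysis and some wording. The companion analysis will carry more mode misclassification and some incomplete days, which is why it stands beside the valid-marked analysis and does not replace it. The article does not say whether unedited records are kept. If they are not, the companion analysis removes the dependence on the mark only, and the edit counts, where the app logs them, become the sole evidence on editing.

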#### Health related quality of life

Health related quality of life will be assessed using the commonly used RAND-36 questionnaire [38, 39]. The RAND-36 consists of 36 items and measures of perceived health across eight domains using a 0–100 scale: 1) physical functioning; 2) bodily pain; 3) role limitations caused by physical health problems; 4) role limitations caused by emotional problems; 5) general mental health; 6) social functioning; 7) energy/fatigue and (8) general health [40].

#### Neighbourhood walkability

Perceived neighbourhood walkability will be assessed at baseline using the Neighbourhood Environment Walkability Scale (NEWS) questionnaire [41–43]. The NEWS scales to assess neighbourhood attributes used in SCAMPI are: (1) residential density; (2) land use mix – diversity; (3) land use mix – access; (4) street connectivity; (5) infrastructure and safety for walking; (6) aesthetics; (7) traffic safety; (8) safety from crime; (9) streets not having many cul-de-sacs and (10) physical barriers to walking. To calculate a perceived walkability index for each participant we will use: residential density, street conductivity and land use mix as previously described [42].

#### App usability and quality assessment

To assess the participant’s use of the app we will collect data on the number of registered days (i.e., days the participants marked as valid in the app) for both groups. For the intervention group the number of weekly goals that were set will be assessed and if goals were met, based on the feedback messages delivered. To assess usability and perceived quality of the TRavelVU Plus app, semi-structured interviews will be conducted in a sub-sample of participants who complete the intervention.

#### Sociodemographic factors

At baseline, participants will complete questions regarding sociodemographic data e.g., sex, age, country of birth, educational attainment, weight and height, and family structure. At follow-up only questions that may have changed and are of relevance for the purpose of the study are repeated, such as if the participant has moved, occupational status or if the participant has access to a bike.

### Statistical analyses

Trial evaluation will be performed with linear mixed model analyses using intention to treat principles. In the statistical models we will use time as a categorical variable (0, 3 and 6 months) with time 0 as a reference group and include an interaction between group and time. The dependent variable is post intervention scores for MVPA (i.e., minutes/day) and the secondary outcomes (e.g., active transportation (minutes/day)). Three-way interactions will be analysed in order to evaluate if the intervention effect was moderated by any of the baseline covariates (e.g., age, sex, educational attainment, neighbourhood walkability or health related quality of life). Missing values on baseline covariates and on follow-up assessments will be imputed simultaneously using multiple imputation with chained equations [m (number of imputations) = 20] [44] taking into account variables of importance for predicting the missing values (e.g., age, sex, country of birth, educational attainment, occupation, season for intervention (i.e., autumn or spring) etc.). Continuous variables will be imputed using predictive mean matching (5 nearest neighbours). Binary variables will be imputed using logistic regression, and multi-categorical variables will be imputed using ordinal logistic regression (if ordered) or multinomial logistic regression (if unordered). Descriptive data over adherence to the intervention will be presented. Per protocol analyses examining effects related to adherence to the intervention (e.g., number of registered days in the app, goals set and achieved) will be conducted using linear mixed models adjusting for age, sex, country of birth (Sweden/not Sweden), educational attainment, occupation and season for intervention. As in the primary analysis, time, group and time-group-interactions will also be included. Sensitivity analyses concerning deviations from the missing at random assumption will be performed using delta-adjustment [45]. Statistics Sweden will provide summary statistics for responders and non-responders regarding age, sex, country of birth, education level and area of residence. All *p*-values < 0.05 (two-sided) will be regarded as statistically significant.

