### Sample size and power considerations

A total of 200 participants (100 in each group) completing follow-up will provide 80% power (α = 0.05) to detect a 10 min difference in MVPA (e.g., 35 versus 45 min/day) assuming a standard deviation of 25 min [31]. Assuming about 20% drop-out rate between baseline and follow-up 250 participants will be enrolled in the study [32]. We will continue to sample until this goal has been reached. Based on our previous experience we estimate that 5000 randomly selected subjects will provide us with the sample requested when considering loss to follow-up and subgroup analyses [33].

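### The primary MVPA model is stated inconsistently, so the month-3 contrast is not fixed; one baseline-adjusted model would settle it and gain precision for a change of wording

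*Protocol article*

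**What the plan says.** The Statistical analyses section describes the primary model in two adjoining sentences. The first says "we will use time as a categorical variable (0, 3 and 6 months) with time 0 as a reference group and include an interaction", the interaction being that of group with time. The second says "The dependent variable is post intervention scores for MVPA (i.e., minutes/day) and the secondary outcomes". Later in the section, the per-protocol description refers back to the primary analysis as containing time, group and their interaction, so a group main effect is present and the arms' baseline means are free to differ. The section does not say which coefficient or contrast is the primary test, and does not say how baseline MVPA enters.

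The Outcomes and measures section defines the primary outcome as MVPA at 3 months. The Sample size and power considerations section plans on 100 completers per arm and states that this number "will provide 80% power (α = 0.05) to detect a 10 min difference in MVPA". Its example is a pair of levels, 35 and 45 min/day, and it proceeds "assuming a standard deviation of 25 min". It gives no correlation between baseline and follow-up.

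**The concern.** If the dependent variable is post-intervention MVPA only, there are no observations at time 0, and time 0 cannot be the reference level. If time 0 is a level, baseline MVPA is part of the dependent variable. One of the two sentences has to give way.

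The choice matters because different repairs lead to different primary tests:

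- Three visits, month-3 interaction: the difference between arms in mean change from baseline.
- Three visits, group effect plus month-3 interaction: the difference in month-3 means.
- Post-intervention visits only, without baseline: again the difference in month-3 means.
- Either layout with baseline MVPA conditioned on, or with a common baseline mean: a baseline-adjusted difference at month 3.

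Under randomisation all of these target the same effect, but they give different estimates and standard errors in any one data set. With the contrast unnamed, the choice could be made after the results are known. The contrast that a reader would most naturally take from the text, the interaction, is also not the one for which the sample size was calculated.

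**Working it through.** **Inputs from the protocol article.** Difference 10 min/day, SD 25, 100 completers per arm, alpha 0.05, 80% power and 20% drop-out (Sample size and power considerations); two-sided testing (Statistical analyses). The example is in levels, so 25 is read as the SD of MVPA at one visit.

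**Assumptions.** The baseline to 3-month correlation ρ is not in the document, so a range is shown. The SD is taken as 25 at both visits. Power is Φ(10/SE − 1.96), with SE = SD × √(2/100).

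**Step 1: reproduce the planned figure.** n per arm = 2 × (1.96 + 0.8416)² × 25² / 10² = 98.1, rounded up to 99; the plan has 100. SE = 25 × √0.02 = 3.54. Power = Φ(10/3.54 − 1.96) = 80.7% (80.4% with the noncentral t). Enrolment = 200/0.80 = 250. The plan's figures reproduce.

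**Step 2: what the interaction tests.** With group, time and group-by-time all free and complete data, the month-3 interaction equals the difference in mean change. Its SD is 25 × √(2(1 − ρ)).

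**Step 3: what the same model gives for levels.** Group effect plus month-3 interaction is the difference in month-3 means. Its SE is 3.54 and its power 80.7% at every ρ.

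**Step 4: baseline-adjusted comparison.** The SD is 25 × √(1 − ρ²). Dropping the group effect at time 0 from the three-visit model gives the same SEs: 3.37, 3.06 and 2.53 at ρ = 0.3, 0.5 and 0.7.

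| ρ (assumed) | Change: SD | Change: SE | Change: power | Adjusted: SD | Adjusted: SE | Adjusted: power |
|---|---|---|---|---|---|---|
| 0.3 | 29.58 | 4.18 | 66.7% | 23.85 | 3.37 | 84.3% |
| 0.4 | 27.39 | 3.87 | 73.3% | 22.91 | 3.24 | 87.0% |
| 0.5 | 25.00 | 3.54 | 80.7% | 21.65 | 3.06 | 90.4% |
| 0.6 | 22.36 | 3.16 | 88.5% | 20.00 | 2.83 | 94.2% |
| 0.7 | 19.36 | 2.74 | 95.5% | 17.85 | 2.53 | 97.7% |

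**Step 5: where the change test reaches 80%.** This requires SE = 10/(1.96 + 0.8416) = 3.57, so SD = 25.24, so 2(1 − ρ) = (25.24/25)² = 1.019 and ρ = 0.49. The noncentral t gives 0.495. If all 125 baselines per arm contribute and 100 per arm are seen at month 3, the threshold falls to about 0.46. At ρ = 0.5 the change test and the level difference have equal SEs.

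**Step 6: relative precision.** Adjusted variance over change variance = (1 − ρ²)/(2(1 − ρ)) = (1 + ρ)/2, which is below 1 for every ρ below 1: 0.65 at 0.3, 0.75 at 0.5, 0.85 at 0.7. Adjusted variance over level variance = 1 − ρ², which is below 1 for every non-zero ρ. Both ratios ignore the trivial cost of estimating the baseline slope.

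**The case against.** The three-visit structure appears twice in the Statistical analyses section: once directly, and once when the per-protocol model is likened to the primary one. The sentence on the dependent variable may be a loose way of naming the outcome measure. That is a fair reading, and it makes the three-visit model the likelier intention. It still leaves open which contrast from that model is primary and how baseline enters.

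Three stronger conclusions are tempting, and the article supports none of them.

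- A reader might infer that the only model that can be fitted is a change-score test. It is not: a model for months 3 and 6 can be fitted once time 0 is dropped, and the three-visit model also delivers the month-3 level difference on which the trial was sized.
- A reader might infer that the trial is underpowered. The sample size reproduces, the correlation is unknown, and above about 0.49 the interaction test has more than 80% power.
- A reader might infer that a free group effect at baseline makes the analysis invalid. In a randomised trial it leaves the estimate unbiased and the type I error intact; the cost is precision.

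It is also fair that a condensed article may leave covariance structure and exact parameterisation to an analysis plan not shown here. Their absence is not criticised. What stands is that the article does state the primary model, and states it in two ways that do not fit together.

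Finally, usable baseline MVPA may not exist for everyone. Randomisation follows completion of baseline measures, but valid-day criteria apply to the accelerometer data, and imputation is planned for missing baseline covariates. Both forms of the fix can accommodate this.

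**Conclusion.** The point holds as an inconsistency of moderate severity. The two sentences cannot both be followed, and the primary month-3 contrast is left open between a change from baseline, a difference in levels and a baseline-adjusted difference.

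The consequence for power depends on the unstated correlation and on equal SDs at the two visits. If the interaction is the test, power runs from 66.7% at a correlation of 0.3 to 95.5% at 0.7. If the level difference is the test, it is 80.7% throughout.

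The gain from baseline adjustment is less conditional. Under equal SDs it beats the change score at every correlation below 1, with 15% to 35% less variance for correlations from 0.7 down to 0.3, and it beats the level difference at every non-zero correlation. The case for change is therefore clarity and precision from data already collected, not a fault in the sample size or in validity.

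**What to change.** Replace the two sentences with one model, in either of two forms:

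1. MVPA at 0, 3 and 6 months as the outcome, with effects for time, group at month 3 and group at month 6, and no group effect at time 0, so that the arms share a baseline mean.
2. MVPA at 3 and 6 months as the outcome, with group, time and their interaction, and with baseline MVPA and its interaction with time as covariates.

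Name the group difference at 3 months as the primary contrast. Use the same form for the secondary outcomes that are measured at baseline, and bring the back-reference in the per-protocol description into line with it.

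The cost is wording in the analysis section. No new data, visits or participants are needed, and the sample size can stay as it is.
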